## Abstract

**Background/Objectives:** Whether remote monitoring reduces mortality in patients with heart failure remains controversial, and research on remote monitoring in South Korea is generally lacking. Therefore, we aim to evaluate the safety and efficacy of remote monitoring for patients in South Korea with severe structural heart diseases who have an implantable cardioverter–defibrillator or cardiac resynchronisation therapy pacemaker/defibrillator. **Methods:** This ReVe study is a multicentre, prospective, observational cohort study in which we will comprehensively evaluate the impact of remote monitoring on cardiovascular-related death and hospital admissions related to pre-existing cardiovascular disease (primary outcomes) and satisfaction with and cost of remote monitoring and the healthcare provider workload (secondary outcomes). Two patient groups are being recruited: (1) Patients in the historical group (*n* = 225) already had a cardiac implantable electronic device implanted after January 2020 and have attended outpatient device check-ups. (2) Those in the initiating group (planned *n* = 225) will undergo cardiac implantable electronic device implantation during this study. In-office visits are scheduled for every 3–6 months. The time/medical cost efficiency and satisfaction index will be evaluated during the 24-month follow-up period. Questionnaires regarding patient satisfaction will be administered every 6 months. **Conclusions:** This is the first prospective study involving patients with structural heart diseases who have implanted high-power cardiac electronic devices. It will provide insights into remote monitoring applications in South Korea and evidence for their use in such patients. It will also provide evidence of the efficacy, safety, and satisfaction with remote monitoring in this population.

## 1. Introduction

Although reports from Western countries have indicated the effectiveness of wireless remote monitoring (RM) of implantable cardiac devices in reducing hospitalisation rates and early diagnosis of disease exacerbation among patients with severe cardiac diseases, such as those who have undergone resynchronisation therapy or defibrillator implantation, its impact on improving survival rates remains debatable [1,2,3]. However, among patients with structural heart disease, continuous wireless monitoring with an implanted cardiac device can not only provide psychological reassurance for both the patient and healthcare providers but also improve the early detection and management of disease progression, which may lead to a reduction in hospitalisation rates and an improvement in prognosis [4]. Therefore, research related to remote monitoring has gained interest, as it may help meet expectations for continued clinical improvements.

Therefore, we designed this study to evaluate the clinical stability and cost-effectiveness of RM in individuals implanted with high-voltage devices who were diagnosed with structural heart disease (such as cardiomyopathies, heart failure with reduced left ventricular ejection fraction [LVEF; below 40%], or congenital heart disease with heart failure) via cardiac ultrasound or computed tomography/magnetic resonance imaging.

South Korea has a unique healthcare system characterised by excellent medical accessibility and well-established healthcare insurance, ensuring that most citizens have access to high-quality medical services [5,6]. The national health insurance system in South Korea offers substantial benefits for patients with severe illnesses. Consequently, for those with heart disease, the out-of-pocket costs are lower than those in other countries, and access to healthcare is exceptionally good. However, the consequence of this national insurance system is that patients are concentrated in university hospitals or other large, tertiary-level hospitals that have high manpower and mobility. In this context, telemedicine is an important aspect of personnel training, which may exacerbate the concentration of patients and the profit gap between hospitals. Therefore, compared with Western countries, South Korea has faced delays in insurance applications and the domestic introduction of new medical technologies and treatments.

As the demand for telemedicine has increased since the coronavirus disease 2019 pandemic, interest in telemedicine for various conditions has also continued to grow [7,8,9,10]. The introduction of RM services for cardiac implantable electronic devices (CIEDs) that had already been validated was accelerated during the lockdown, and their safety has been demonstrated abroad [11,12]. However, domestic medical experts have little experience with RM, which is still not commonly used in primary, secondary, and tertiary medical centres. We reported the first pilot study (the remote care study) on the efficacy, cost-effectiveness, and safety of RM of implantable cardiac devices in Korea [13,14,15]. We noted that RM yielded time-saving benefits with advanced care to the study participants without increasing the rate of adverse clinical events; however, it also increased the clinicians’ workload. The remote care study had a small sample comprising patients without structural heart diseases and pacemakers. Therefore, we could not elucidate the efficacy and clinical safety of RM for patients with severe structural heart diseases. In line with our previous study, we designed a clinical trial to evaluate the hospitalisation rate, cardiocerebrovascular events, cardiac death, and socio-economic efficacy of RM in two groups of patients implanted with high-power devices with severe structural heart diseases. We also aim to provide evidence for the cost and personnel allocation for RM, along with efficiency and patient satisfaction with RM care within the domestic healthcare system.

## 2. Materials and Methods

### 2.1. Study Design

The RemoteVerify (ReVe) study is a multicentre, prospective, observational study that will be conducted at eight university hospitals (St. Vincent’s Hospital, The Catholic University of Korea; Eunpyeong St. Mary’s Hospital, The Catholic University of Korea; Seoul St. Mary’s Hospital, The Catholic University of Korea; Keimyung University Hospital; Kyungpook National University Hospital; Pusan National University Hospital; Yeungnam University Medical Center; Pusan National University Yangsan Hospital) in Korea, targeting 450 patients (each centre will enrol 50 to 70 patients). This sample size was based on the assumption that the 2-year incidence of major adverse cardiac and cerebrovascular events of patients with structural heart diseases is 10% to 15%, with a confidence interval of 95% and a margin of error of 5%. The desired sample size was calculated as 139 to 196 participants per group using G*Power version 3.1.9.7 [16], and similar patients are needed in the two groups that differ in the timing of RM application. Considering an anticipated 10% loss to follow-up during the study period, the total number of participants needed for this study was determined as 442. We rounded this number up to 225 per group. An interim analysis will be conducted using the variables collected by the planned patient enrolment period (24 months). A second interim analysis will be conducted after at least 12 months of follow-up data have been collected. The final analysis will be performed at the study endpoint after all participants have completed the 24-month follow-up. Starting from the interim analysis, subgroup analyses will be conducted based on the type of underlying heart disease (hypertrophic cardiomyopathy/ischaemic cardiomyopathy/dilated cardiomyopathy/others) and the left ventricular ejection fraction (LVEF; <30%, 30–45%, >45%).

Eligible study participants will need to meet the following criteria: patients (1) aged 20 years or older with (2) an LVEF below 40% or a structural heart disease confirmed via cardiac imaging, (3) an implantable cardioverter–defibrillator (ICD) or a cardiac resynchronisation therapy (CRT) device compatible with Biotronik Ltd. (Berlin, Germany) wireless monitoring devices, and (4) a predicted life expectancy of more than 6 months, (5) capable of understanding and completing the simple consent form, and (6) never having been enrolled in clinical trials that involve RM before. Patients will be informed that if they want to withdraw their consent to this study, they can stop participating in this clinical trial, and their data will be collected until the withdrawal date. Exclusion criteria are as follows: (1) patients with a life expectancy of 6 months or less, (2) patients with cognitive impairment who are unable to understand the information regarding wireless monitoring or who are unable to provide consent, and (3) patients currently participating in another clinical trial that may be affected by the implementation of wireless monitoring. Patients who have previously participated in clinical trials, those who are currently participating in a clinical trial that the investigator judges will not affect or be affected by this trial, and those who are participating in other observational studies are eligible for this study. If the patient wishes to discontinue participation in the study or dies within 6 months of participation (to be noted separately), they will be considered withdrawn from the study.

Informed consent will be obtained from each participant included in the study. Details of the study protocol are available at ClinicalTrials.gov (study ID: NCT05971225). Patient enrolment started in November 2023 at two centres (40 and 10 patients were enrolled in St. Vincent’s Hospital and Eunpyeong St. Mary’s Hospital, respectively, as of 1 August 2024) after Institutional Review Board approval (VC23DIDI0148; approval date: 11 July 2023) and will continue until October 2025. Follow-up data will be acquired for 24 months after enrolment. We plan to collect the final data in December 2027, and the results of the ReVe study will be published in 2028.

The other six participating centres are obtaining approval from their Institutional Review Boards (IRBs). The IRBs will independently monitor the study protocol and process and conduct audits every 6 months from the enrolment of the first patient. The investigation conforms with the principles outlined in the Declaration of Helsinki and is supported by funding from Biotronik.

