### 2.3. Statistical Analysis

We will compare outcomes before and after RM via paired *t*-tests in the historical group. We will compare the clinical-, RM-, and device-related variables via independent samples *t*-test between the historic and initiating RM groups. Tests for normality will be provided. If data is non-normal, then *t*-tests and means/standard deviations should be avoided, and Mann–Whitney/Wilcoxon and medians/interquartile ranges should be preferred. For the *t*-tests, we will reject the null hypothesis when the two-sided *p*-value is less than 5%. For the analysis of patient baseline data, continuous variables will be presented as means and standard deviations and analysed using *t*-tests or Wilcoxon rank-sum tests. Categorical variables will be presented as frequencies and percentages. For the analysis of satisfaction with the survey, paired *t*-tests (parametric test) or Wilcoxon signed-rank tests (non-parametric test) will be performed. For surveys conducted only after monitoring, ordinal variables will be analysed using the Mann–Whitney U test, and continuous variables will be analysed using chi-square tests. For patients not completing the follow-up, censoring will be based on the last data collected. Cumulative event probabilities will be estimated with adverse health outcomes, such as patient deaths, inpatient admissions, and MACCEs. Hazard ratios and 95% confidence intervals will be generated with Cox proportional hazards models. For subgroup analyses, the interaction term between the prespecified groups, based on the type of underlying heart disease and LVEF, will be evaluated for the primary outcome. Because of the interim analyses, we will adopt the O’Brien–Fleming method for statistical corrections. For all analyses, we will use two statistical software packages: Stata, version 18 (StataCorp LLC, College Station, TX, USA), and R, version 4.05 (R Foundation for Statistical Computing, Vienna, Austria).

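### The sample size gives each group a 5-point margin for its own MACCE proportion; that margin does not carry over to the planned comparison of the historical and initiating groups, for which no difference or power is stated

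*Protocol article*

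**What the plan says.** Section 2.1 (Study Design) of the protocol article gives the whole basis of the sample size:

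- **Event rate:** one range for the study population, "2-year incidence of major adverse cardiac and cerebrovascular events of patients with structural heart diseases is 10% to 15" (per cent).
- **Criterion:** "with a confidence interval of 95% and a margin of error of 5" (per cent).
- **Result:** "The desired sample size was calculated as 139 to 196 participants per group using G*Power version 3.1.9.7".
- **Loss:** "Considering an anticipated 10% loss to follow-up during the study period, the total number of participants needed for this study was determined as 442".
- **Target:** "We rounded this number up to 225 per group", that is 450 in total.

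The same section says that the two groups should be similar and differ in when remote monitoring (RM) starts. It states no between-group difference, hazard ratio or power.

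Section 2.2 (Data Collection) then sets the historical group against the initiating group to see whether hospitalisation improves with RM. It also says that MACCEs will be determined in the initiating group for comparison. Section 2.3 (Statistical Analysis) adds between-group tests, "We will compare the clinical-, RM-, and device-related variables via independent samples" t-tests, with rejection at a two-sided 5% level.

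**The concern.** A size quoted per group, in a two-group study that plans between-group tests, is easily read as adequate for the comparison. The inputs in section 2.1 cannot support that reading, because a confidence level and a margin for one proportion say nothing about the difference between two. The sampling error of a difference combines the errors of both groups. With equal sizes and equal rates it is larger by a factor of √2.

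At stake is how the comparison is read. A reader who takes the 5-point margin to apply to the group difference will think it more precise than it is. If the difference is not significant, nothing in the printed plan tells the reader how large a true difference would still be compatible with the data.

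Separately, the stated total of 442 cannot be obtained from 196 per group and a 10% loss.

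**Working it through.** **1. Reproducing the plan's figures.** The inputs from section 2.1 are p = 0.10 and 0.15, z = 1.96 and margin d = 0.05. The formula for one proportion is n = z²·p(1−p)/d².

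- p = 0.10: 3.8416 × 0.09 / 0.0025 = 138.3, so 139.
- p = 0.15: 3.8416 × 0.1275 / 0.0025 = 195.9, so 196.

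Both printed figures are matched exactly, so this is the calculation that was done. It has no term for a second group, a difference or power.

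**2. Precision at the planned size.** 225 per group less 10% is 225 × 0.9 = 202.5, taken as 202 evaluable.

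| Quantity | Formula | Rate 10% | Rate 15% |
|---|---|---|---|
| One group's rate | 1.96·√(p(1−p)/202) | 4.1 points | 4.9 points |
| Difference, both groups at the same rate | 1.96·√(2p(1−p)/202) | 5.9 points | 7.0 points |

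If all 225 per group were evaluable, the half-width for a difference would be 5.5 to 6.6 points. To hold 5 points for a difference, the per-group size would be 2 × 138.3 = 276.6, so 277 (at 10%), to 2 × 195.9 = 391.8, so 392 (at 15%).

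**3. Power, on an assumed contrast.** The protocol names no group difference. For illustration, take the two ends of its range as the two group rates, 15% versus 10%, with a two-sided 5% level. The mean rate is 0.125. The null term is √(2 × 0.125 × 0.875) = 0.4677, and the alternative term is √(0.09 + 0.1275) = 0.4664.

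- 202 per group: (0.05·√202 − 1.96 × 0.4677)/0.4664 = −0.44, power about 33%.
- 225 per group: (0.05·√225 − 1.96 × 0.4677)/0.4664 = −0.36, power about 36%.
- For 80% power: (1.96 × 0.4677 + 0.8416 × 0.4664)²/0.0025 = 686 per group, before loss.

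**4. The total.** The inputs are 196 per group and 10% loss.

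- Dividing by the retained fraction: 196/0.9 = 217.8, so 218 per group and 436 in total.
- Multiplying by 1.10: 392 × 1.10 = 431.2, so 432.
- To reach 442 from 392 needs a loss of 1 − 392/442 = 11.3%. Alternatively it needs about 199 per group (398/0.9 = 442.2).

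The printed total is 6 above 436, and 450 exceeds all of these figures.

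**The case against.** The other side has a good case, and much of it stands.

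- **Precision sizing is legitimate and disclosed.** This is an observational cohort. Its primary endpoint is MACCE after RM together with the variables that predict it. Section 2.1 names the interval and the margin and claims no power. Read literally, the figures per group are correct for each group's own rate. This stands, so the point is confined to the comparison in section 2.2 and the between-group tests in section 2.3.
- **The Cox models may not compare the groups.** A reader might infer that the hazard ratios in section 2.3 contrast historical with initiating patients. The text does not say so; they could concern predictors of MACCE. No detectable hazard ratio is therefore argued here. Likewise, the t-test sentence in section 2.3 does not name MACCE. The intention to compare MACCE and hospitalisation comes from section 2.2.
- **No equivalence or safety claim is planned.** A reader might infer that p > 0.05 will be reported as safety. No sentence says that. The request to rule it out is a precaution.
- **15% versus 10% is not the protocol's contrast.** Those figures are one range of uncertainty for the whole population. The power figures show scale only and do not establish that 450 patients are too few.
- **The before-and-after RM comparison is separate.** It is a paired analysis within the historical group, and the two-group figures above do not describe it.
- **The total is harmless.** A reader might take 442 as a sign of a shortfall. It errs upward and the 450 target replaces it.

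What the objection does not remove is that the comparison in section 2.2 is planned, and that the only precision printed is for something else.

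**Conclusion.** The point holds in a limited form. The 139 to 196 per group are sizes for estimating one proportion to within 5 points, reproduced exactly. They are valid for each group separately and do not size the comparison of the historical and initiating groups.

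At about 202 evaluable per group, the 95% half-width for a difference is 5.9 to 7.0 points. This assumes equal rates of 10% or 15% in both groups, a 10% loss and the usual normal approximation. The power of about 33% (36% with no loss) depends wholly on an assumed 15% versus 10%.

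The total of 442 is a minor discrepancy. The printed inputs give 436, and nothing in the design depends on the gap. The documents do not support a conclusion that the study is too small for its descriptive aim, that recruitment falls short, or that a false safety claim is planned. The restatement is worth making because it is cheap and affects how the group comparison will be read.

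**What to change.** Keep 450 patients and restate the basis in section 2.1, with a matching sentence in section 2.3:

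- The size was chosen for precision. With about 202 evaluable per group, each group's 2-year MACCE proportion is estimated to within 4.1 points (at 10%) to 4.9 points (at 15%).
- The corresponding 95% half-width for a difference between the groups is 5.9 points (both 10%) to 7.0 points (both 15%).
- Between-group comparisons of MACCE and hospitalisation are not powered and will be reported as estimates with 95% confidence intervals. A non-significant difference will not be read as equivalence or safety.
- Correct the total to 436 (218 per group, rounded up to 225), or show how 442 was obtained.

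The cost is rewording only, with no extra patients and no change to data collection. The drawback is that the precision stated for the comparison is less favourable than the 5 points a reader would now assume.

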In this study, we may also use the successor model of the CM family. The package provided to participants will consist of the CM and a power supply module. The CM receives information from the paired CIED once daily, typically at night. The transmitter is used for communication with the CIED, and the data received from the device are encrypted and sent to the company website (www.biotronik-homemonitoring.com/, accessed on 6 February 2025) via the data module. Healthcare providers receive an alert from the website when the device detects a change in the patient’s heart rhythm, identifies issues with the device itself, or prompts a reminder for periodic, overall CIED check-ups.

The ReVe study will be the first prospective multicentre study in South Korea in which the following conditions are fulfilled:(1)Collecting data from all visits or admissions during the study period, classified as device-related, patient cardiovascular condition-related, or non-cardiovascular condition-related events. These visits will also be categorised as either physician-driven (RM-based) or patient-driven hospital visits.(2)Analysing MACCEs, such as myocardial infarctions/cerebrovascular accidents, thromboembolic events, exacerbation of heart failure, admissions due to cardiac causes, cardiac-related mortality (as a proportion of overall mortality), and other cardiac events.(3)Collecting and analysing data on RM variables weekly, including thoracic impedance and lead sensing, to elucidate their correlation with disease progression, admission, and mortality.(4)Evaluating the staffing/time requirements for RM using electronic medical records (log-in and log-out times are recorded).(5)Analysing and comparing patient satisfaction questionnaires after RM every 6 months (Table 1) via telephone or during office visits (between the historical and initiating groups). The questionnaire evaluates the efficacy of RM and the perceived quality of care due to RM. It contains nine questions with five answer categories each (strongly agree, agree, neutral, disagree, and strongly disagree).

Questions (1) to (3) contain the primary outcomes, and (4) and (5) include the secondary outcomes. These are summarised in Figure 1.

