Patients with CIEDs, except those on warfarin or those with other relevant medical issues (followed up on other clinic consultation schedules), are scheduled for routine clinical follow-ups every 3–6 months. Patient satisfaction surveys are scheduled every 6 months to assess changes in satisfaction levels over time and explore varying trends across device types (‘Survey on telehealth patient experience’ by [name], 2023 [15], modified Korean version 1.3; Table 1). The study is summarised in Figure 1, and the process of the study is also available in Supplementary Table S1.

The primary endpoint will be any MACCE after RM (cardiovascular-related death and hospital admissions related to pre-existing cardiovascular disease), defining variables that are predictive of MACCE and unexpected hospital visits during RM. The secondary endpoints will be patient satisfaction with the time, cost, and quality of care after adopting RM (determined via questionnaires on a 6-month basis) and the staffing/time requirements during RM (measured using electronic medical records).

All files and data generated during the study are stored in a safety deposit box or as copied files secured with passwords accessible only to the investigators. Because this study includes personal identifiers and sensitive information, the data will not be openly accessible. Anonymised study data will be made available to researchers upon reasonable request after the study results are published.

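### Classing deaths in the first 6 months as withdrawals contradicts the primary endpoint and, if carried into the analysis, understates mortality by about a quarter and MACCE modestly

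*Protocol article*

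**What the plan says.** The rule on early deaths stands in section 2.1 (Study Design), after the eligibility criteria. A patient who chooses to stop, or who "dies within 6 months of participation (to be noted separately), they will be considered withdrawn from the study", is handled in the same sentence. For patients who withdraw consent, the same section says that "their data will be collected until the withdrawal date".

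Section 2.2 (Data Collection) defines the endpoint: "The primary endpoint will be any MACCE after RM (cardiovascular-related death and hospital admissions related to pre-existing cardiovascular disease". It sets no start later than the start of remote monitoring (RM) and excludes no early period. The outcome list in that section also includes "cardiac-related mortality (as a proportion of overall mortality".

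Section 2.3 (Statistical Analysis) gives the censoring rule: "For patients not completing the follow-up, censoring will be based on the last data collected". The next sentence reads: "Cumulative event probabilities will be estimated with adverse health outcomes, such as patient deaths, inpatient admissions, and MACCEs". Cox models follow. No sentence says how the early deaths that are noted separately enter any of these analyses.

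**The concern.** Cardiovascular death is one of the two components of the primary endpoint, and deaths are also analysed in their own right. Yet for the first quarter of follow-up the article gives death the same status as a voluntary exit. If a withdrawn patient is a non-completer, and non-completers are censored at their last data, a cardiovascular death on day 100 would be a censored time and not an event. If withdrawn patients are left out altogether, the death is lost as well.

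The rule is hard to read as a mere label for the end of participation, because that would apply to a death at any time. This one singles out the first 6 months.

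At stake are the absolute MACCE incidence and mortality. The study is meant to report on the safety of RM and to inform guidelines and insurance standards. Dropping early deaths pushes both rates down.

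**Working it through.** **Inputs from the article.** Follow-up: "Follow-up data will be acquired for 24 months after enrolment" (section 2.1), so 6 months is 6/24 = 25% of it. Planning value for 2-year MACCE incidence: 10% to 15% (section 2.1). Planned enrolment: 450 (section 2.1).

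**Inputs not in the article, therefore assumed.** A constant hazard over 24 months; a share *f* of first primary events that are cardiovascular deaths, taken as 10%, 25% and 50%; a 24-month cardiovascular mortality *D*, taken as 3%, 5% and 10%.

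**1. The plan's own figure.** The precision formula n = 1.96² × p(1 − p) / 0.05² gives 138.3, so 139, at p = 0.10 and 195.9, so 196, at p = 0.15. This matches the stated 139 to 196 per group. Inflating 196 for 10% loss gives 196/0.9 = 217.8, so 218 per group or 436 in total. The article says 442, which is 1.4% more, and 450 covers both. The point here does not rest on this figure; the step only confirms that 10% to 15% is the planning range.

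**2. The passages side by side.**

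| Section | Statement | Consequence for a cardiovascular death on day 100 |
|---|---|---|
| 2.1 | Death within 6 months is a withdrawal | Patient does not complete follow-up |
| 2.3 | Non-completers are censored at last data | Censored, unless an exception exists; none is stated |
| 2.2 | Cardiovascular death after RM is a primary event | Event |
| 2.3 | Cumulative probabilities of deaths and MACCEs are estimated | Event |

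The first two rows conflict with the last two.

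**3. Share of events in the first 6 months.** With 2-year risk P, the yearly hazard is λ = −ln(1 − P)/2 and the 6-month risk is 1 − exp(−0.5λ).
- P = 10%: 6-month risk 2.60%, which is 26.0% of the 2-year risk; 11.7 of 45 events in 450 patients.
- P = 15%: 6-month risk 3.98%, which is 26.5% of the 2-year risk; 17.9 of 67.5 events.

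**4. Cardiovascular mortality if early deaths are censored.** No deaths are counted in the first quarter, so the estimate is 1 − (1 − D)^0.75.

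| True D | Estimated | Relative loss | Deaths not counted in 450 |
|---|---|---|---|
| 3% | 2.3% | 24.7% | 3.4 |
| 5% | 3.8% | 24.5% | 5.7 |
| 10% | 7.6% | 24.0% | 11.7 |

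The last row is an outer bound: 45 cardiovascular deaths would equal all the events expected at 10% incidence.

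**5. Composite if early deaths are censored.** Only first events that are cardiovascular deaths are lost. The estimate is 1 − exp(−[0.5λ(1 − f) + 1.5λ]), and the number lost is 450 × 6-month risk × f.

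| f | True 10%: estimate (lost) | True 15%: estimate (lost) |
|---|---|---|
| 10% | 9.8% (1.2) | 14.7% (1.8) |
| 25% | 9.4% (2.9) | 14.1% (4.5) |
| 50% | 8.8% (5.8) | 13.3% (9.0) |

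**6. If withdrawal means exclusion.** With d = 6-month risk × f, the estimate is (P − d)/(1 − d). To one decimal this gives the same values as the table in step 5. The result therefore does not depend on which of the two meanings applies.

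**The case against.** The strongest reply is that the censoring step is inferred. The sentence in section 2.1 sits among eligibility and consent text and may describe participation only. In ordinary time-to-event practice a censoring rule applies to patients without an event. Section 2.3 names deaths and MACCEs as events straight after the rule, and the parenthesis about separate noting may be how a fuller document keeps these deaths in. This stands in part: no sentence says that early deaths are censored, and the point has to be conditional. It does not remove the conflict. The article states a rule that groups early deaths with voluntary exits, and recording a death separately is not the same as counting it.

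A second reply concerns size, and it stands. The composite also counts cardiovascular admissions. A patient admitted before an early death keeps that first event if data up to withdrawal are used. The composite falls by about 0.2 to 1.7 percentage points, well inside the ±5 points for which the study was sized.

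Three stronger readings are tempting, and the document does not support them:
- **All reclassified deaths are lost from the composite.** A reader might set the 3 to 12 deaths in step 4 against the 45 to 68 expected MACCEs. Those are deaths, not first events; the loss of first events is about 1 to 9.
- **The rule biases the comparison between groups.** Initiating patients enter around implantation, and historical patients have already lived with the device for a time, so unequal early mortality is possible. The article gives no figure for it. Both groups receive RM, so an understated absolute rate does not by itself favour either group.
- **The rule re-applies the life-expectancy criterion after the outcome is known.** The shared 6-month threshold is suggestive, but the article gives no rationale.

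**Conclusion.** The point holds as a contradiction that must be reconciled. Section 2.1 makes early death a withdrawal, while sections 2.2 and 2.3 need it as an event. If the withdrawal rule is carried into the analysis by censoring or by exclusion, the bias in absolute rates is downward in every scenario examined. It is substantial for cardiovascular mortality, at about a quarter in relative terms. It is modest for the primary composite.

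These sizes rest on a constant hazard and on assumed death rates and death shares, because the article gives none. If deaths cluster early, the loss is larger; if they come late, it is smaller. That early deaths will in fact be censored, and that the groups will be affected unequally, are not established.

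**What to change.** In section 2.1, remove death from the withdrawal sentence. State that every cardiovascular death after the start of RM, including one in the first 6 months, is a primary-endpoint event on its date, and that all deaths count in the mortality analyses.

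In section 2.3, limit the censoring rule to consent withdrawal, loss to follow-up and the end of follow-up. For cumulative incidence of the primary endpoint, treat non-cardiovascular death as a competing event (Aalen-Johansen estimator). In a cause-specific Cox model such a death is censored at the time of death, and the text should say so, so that the two statements do not clash. An analysis with a 6-month landmark may be kept as a sensitivity analysis.

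The cost is a short protocol amendment, to go through the review boards of the participating centres. Early deaths are already to be noted; only their date and cause need to be available for analysis. The reported event rate may become slightly less favourable.
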